**Others**								
Starting time of treatment		●						
Combination therapy		●	●	●	●	●	●	●
Issue medications and diary cards		●	●	●	●	●		
Recycle medications and diary cards			●	●	●	●	●	
eCRF	●	●	●	●	●	●	●	●

*SGRQ* The St George's Respiratory Questionnaire, *CAT* COPD assessment test, *HCG* Human chorionic gonadotropin, *NGHX* Urine dry chemical analysis, *eCRF* Electronic case report form

^a^The time window of follow-up is ± 3 days, while the additional visit is ± 1 day;

^b^For additional visits, if subjects have an acute exacerbation, an additional visit will be taken on the first day of the exacerbation;

^c^The time window of screening is -28 ~ 0 days, and Day 0 is the day on which medication is started. During the screening period, the results of HCG, GHb, NGHX, lung function, blood routine, and serum biochemicals can be accepted within 7 days;

^d^Demographics, including age, gender, height, weight, marital status, ethnic origin, etc.;

^e^General clinical information, including medical history, course of the disease, number of exacerbations within the past year, etc.,

^f^Constitution of TCM [23]: based on the Classification and Determination of Constitution in TCM(ZYYXH/T157-2009) released by the China Association of Chinese Medicine;

^g^For the exploratory assessments, the chief unit is required to conduct tests every visit, while others are required on Day 0, Week 24, Week 52, and additional visits. Sputum, throat swabs, and blood samples are detected and analyzed by the central laboratory and the results are uniformly recorded, but not included in the CRF

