### Sample size

According to the results of the previous study [15], the mean difference in CAT scores between the YPF group and the control group was 2.2, and the combined standard deviation was 6.2184. The sample size was calculated accordingly, with an α risk of 0.05 and a β risk of 0.2 in a two-sided contrast. This study required a minimum of 252 subjects. Allowing for 20% attrition, a total sample size of 316 subjects was required, 158 in the treatment group and 158 in the control group.

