### Inclusion criteria

Aged 40 to 80 years, male or female;Patients meet the diagnostic criteria for COPD (Guidelines for the diagnosis and management of chronic obstructive pulmonary disease (revised 2021 version) [24].)Patients clinically diagnosed with moderate to severe COPD (based on the 2021 GOLD guidelines), with airflow limitation including the following: a postbronchodilator fixed ratio FEV1/FVC ≤ 70%, 30% ≤ FEV1 < 80% predicted;The single score of expectoration ≥ 1 point;Patients with a history of exacerbations in the past year: ≥ 2 moderate acute exacerbations or ≥ 1 severe acute exacerbation;Patients were in stable condition in the past 4 weeks, without respiratory tract infection and AECOPD;Volunteered to participate in the trial, and signed the written informed consent.

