#### Efficacy analysis

Different analysis methods will be adopted according to the variable type of efficacy indicators. Specifically, Fisher's exact test will be used to compare categorical variables, including the annualized rates of moderate or severe COPD exacerbations, all-cause admission rate, admission rate due to acute exacerbation, the proportion of patients with an SGRQ response, annualized rates of acute exacerbation of COPD with different severity, and the frequency of first-aid drug use. The duration and interval of AECOPD will be tested by the log-rank test, and the Cox proportional-hazards model will be used to calculate the hazard ratio (HR) and 95% confidence interval (CI). The changes in the CAT score, the SGRQ score, the clinical symptom score, and the single clinical symptom score will also use the log-rank test and the Cox proportional-hazards model for analysis.

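### Fisher's exact test, assigned to the exacerbation and admission rates, cannot use the past-year exacerbation count recorded at screening, so precision is lost on these secondary outcomes

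*Protocol article*

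**What the plan says.** Four parts of the protocol article bear on this point.

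- **Analysis.** The Efficacy analysis section treats the event rates as categorical variables and assigns them Fisher's exact test, "including the annualized rates of moderate or severe COPD exacerbations, all-cause admission rate, admission rate due to acute exacerbation" and the severity-specific exacerbation rates among them. Duration and interval of exacerbations get a log-rank test and a Cox model. No covariates are named for that model.
- **Outcome definition.** Outcome measurements defines the moderate or severe exacerbation rate, and both admission rates, as the number of events over 52 weeks divided by the number of participants in the group.
- **Baseline data.** Table 1, footnote e, lists "number of exacerbations within the past year" among the general clinical information taken at screening. The Inclusion criteria set a floor on that history: "≥ 2 moderate acute exacerbations or ≥ 1 severe acute exacerbation".
- **Use of baseline factors.** Randomization is stratified by blood eosinophils at a single cut-off. Subgroup analyses gives eosinophils and TCM constitution a role. Exacerbation history appears in neither section.

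**The concern.** A patient's recent exacerbation count is an obvious candidate predictor of the next year's count, and the trial relies on it to select patients. The entry rule sets only a minimum, so a patient with one severe event and a patient with many events enter the same comparison. A count model could absorb part of that variation. Fisher's exact test cannot: it needs a two-by-two table with each patient counted once, and it has no place for a covariate or for follow-up time.

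At stake is precision on outcomes for which the article states no power. The sample size rests on the CAT score alone. Yet exacerbation reduction is the earlier result cited in the Background (32.3%), and the Discussion says the microecology and immunity work is meant to help explain it.

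**Working it through.** **1. The plan's own figure.** Inputs from the Sample size section: "the mean difference in CAT scores between the YPF group and the control group was 2.2", "the combined standard deviation was 6.2184", "with an α risk of 0.05 and a β risk of 0.2 in a two-sided contrast".

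n per arm = 2 × (1.960 + 0.8416)² × 6.2184² / 2.2² = 2 × 7.849 × 38.67 / 4.84 = 125.4, so 126 per arm and 252 in total. The plan agrees: "This study required a minimum of 252 subjects". Then 252 / 0.80 = 315, or 316 with equal arms, as stated. The calculation reproduces, but it concerns CAT and says nothing about power for exacerbations.

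**2. Can the named test use the history?** The outcome is a count per patient that can exceed one. Fisher's test requires each patient to be reduced to event or no event. History cannot enter until a different method is chosen. The Cox model could take it, and the text does not say whether it does.

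**3. Size by formula.** The documents give no control rate, dispersion or prognostic strength, so these are assumptions: control rate μ0 of 0.8 to 1.8 per year, dispersion k of 0.5 to 1.0, and history explaining a share R² of 10% to 30% of between-patient variation. The rate ratio is 1 − 0.323 = 0.677, which reads the Background's risk reduction as a rate ratio. With n = 158 per arm and μ1 = 0.677 μ0:

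Var(log RR) = (1/n) × [(1/μ0 + k) + (1/μ1 + k)], with k replaced by k(1 − R²) after adjustment.

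Example with μ0 = 1.2 and k = 1.0:
- Unadjusted: (0.833 + 1 + 1.231 + 1) / 158 = 0.02572, SE 0.1604. Then z = 0.390 / 0.1604 − 1.960 = 0.472, power 68.2%.
- R² = 30%: (0.833 + 0.7 + 1.231 + 0.7) / 158 = 0.02193, SE 0.1481, power 75.0%. Variance falls by 0.6 / 4.064 = 14.8%.

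| μ0 | k | Unadjusted power | R² = 10% | R² = 30% | Variance reduction, R² = 10% to 30% | Any event yes/no |
|---|---|---|---|---|---|---|
| 0.8 | 0.5 | 67.8% | 68.9% | 71.1% | 2.4% to 7.3% | 49.8% |
| 0.8 | 1.0 | 58.4% | 60.1% | 63.8% | 3.9% to 11.8% | 39.4% |
| 1.2 | 0.5 | 80.0% | 81.3% | 83.9% | 3.3% to 9.8% | 53.9% |
| 1.2 | 1.0 | 68.2% | 70.3% | 75.0% | 4.9% to 14.8% | 40.8% |
| 1.8 | 0.5 | 88.9% | 90.1% | 92.5% | 4.2% to 12.6% | 54.0% |
| 1.8 | 1.0 | 76.1% | 78.6% | 83.7% | 5.9% to 17.8% | 39.5% |

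Adjustment adds about 1 to 8 points of power. At 126 per arm, the number left after the planned attrition, unadjusted power is 49% to 81% and the gain is again about 1 to 8 points. The last column is a chi-square approximation to testing any exacerbation yes/no (exact Fisher is somewhat lower). Reducing counts to yes/no costs more than omitting history.

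**4. Size by simulation.** Patient rates were gamma-distributed (population mean 1.0 to 1.2 per year, dispersion 0.5 to 1.2). The prior-year count was filtered by the entry rule with 25% of events severe; the rate ratio was 0.75, with 158 per arm and about 300 replicates per scenario. Negative binomial models with and without log prior count were compared. In repeated independent runs the ratio of unadjusted to adjusted variance was about 1.05 to 1.07 at low heterogeneity, 1.14 to 1.15 in the middle and 1.24 to 1.26 at the high end. Power rose by 2 to 12 points. When each patient's rate was allowed to drift between years, the ratio was about 1.09 and the gain 0 to 5 points. The Monte Carlo standard error of each power figure is about √(0.66 × 0.34 / 300) = 2.7 points, so the smallest gains are within noise. The truncation at entry is already in these results: the SD of log prior count after filtering was still 0.48 to 0.57.

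**The case against.** The strongest reply is that covariate lists belong in the statistical analysis plan, which is not shown, and that a journal article condenses. **For the Cox model this stands.** A reader might infer that history is left out of every exacerbation analysis, but the text is only silent about Cox covariates and silence is not exclusion. Nor does the article assign a Cox model to time to first exacerbation; it assigns one to duration and interval. **For the rates the reply fails**, because the article names a test that cannot take a covariate.

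Second, the larger defect is Fisher's test on event counts, and the covariate depends on correcting that. This is right, and the fix below is ordered accordingly. The gains in steps 3 and 4 compare two count models, neither of which is planned, so they are not the power of the present plan. But replacing the test would not by itself add the covariate.

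Third, the inputs are assumed, and the simulation's main case is favourable: stable patient rates, exact recall, no dropout. This stands, and the real gain is more likely in the lower or middle part of the range.

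Fourth, a reader might take these for the trial's most important secondary outcomes, since the moderate or severe rate is listed first. The article states no ranking, and its Discussion pairs symptom scores and SGRQ with CAT.

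Finally, a reader might infer bias from an unadjusted chance imbalance in history. Randomization does not support that: a valid unadjusted test already allows for chance imbalance in its type I error.

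**Conclusion.** The point holds for the exacerbation and admission rates: the assigned test rules out a baseline predictor that the trial already collects. For the Cox analyses it can only be said that the covariates are not stated.

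Measured against an unadjusted count model, adjustment is worth roughly 5% to 25% more patients with a population rate of 1.0 to 1.2 per year, dispersion 0.5 to 1.2 and rate ratio 0.75. The formula, on its own assumed ranges, gives a variance reduction of 2% to 18%. Both rest on inputs the documents do not supply, and drift in patient rates, imperfect recall or dropout would shrink the gain. It is an efficiency improvement on secondary outcomes without stated power. It corrects no bias and leaves the CAT sample size untouched.

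**What to change.** 1. Replace Fisher's exact test for the moderate or severe, severity-specific and admission rates with a negative binomial model, using log follow-up time as offset.
2. In that model prespecify two covariates: prior-year exacerbation count (log, or grouped 1 / 2 / 3 or more) and the eosinophil stratum. The entry rule guarantees at least one prior event, so the log is always defined.
3. Use the same covariates in any Cox model for exacerbation timing, and say so in the text.
4. Report the unadjusted result as a sensitivity analysis.

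All of this should be fixed before the data are unblinded, because the article has the analysis performed after unblinding and a covariate chosen then would be open to challenge.

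The cost is small but more than a line of wording: the test itself has to change first, and there is slightly more analysis work. No new data are needed. The history rests on recall or records; error there reduces the gain but does not bias a randomized comparison.

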**Methods/design:**

This is a prospective, multicentre, randomized, double-blind, placebo-controlled clinical trial. A total of 316 eligible subjects with moderate to severe COPD will be randomized 1:1 to receive YPF or placebo. Participants will receive either YPF or a placebo at 5 g three times daily for 52 weeks. The primary outcome will be the change in the COPD Assessment Test (CAT) score after 52 weeks of treatment. Secondary outcomes will include changes in the St George's Respiratory Questionnaire (SGRQ) score and clinical symptom score, among others. Outcomes will be measured at each visit. The study will continue for 52 weeks and will include six visits to each subject (at day 0 and weeks 4,12,24,36 and 52). In the event of exacerbations, subjects will be required to go back to the hospital once on the first day of exacerbation or when their condition permits.

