Traditional Chinese Medicine (TCM) is the greatest treasure trove waiting to be discovered by modern medicine. YuPingFeng (YPF), one of the classic TCM formulas with a tonic effect, is composed of Astragali Radix, Atractylodes Macrocephala Koidz, and Radix Saposhnikoviae. Recent pharmacological studies have shown that YPF can activate mucosal immunity, resists hormone-induced immunosuppression, and is recommended to be used in the treatment of stable COPD [13, 14]. A multicentre, randomized, double-blind, placebo-controlled clinical study we conducted confirmed that the combination of conventional treatment with YPF granules for 52 weeks significantly reduced the risk of acute exacerbations by 32.3% in moderate-to-severe COPD patients [15], but did not investigate the mechanism. Some small sample sizes or observational trials have shown that this drug may regulate immune function, improve lung function, and improves the quality of life [16, 17], but high-quality evidence-based evidence is still lacking. In recent years, the heterogeneity of AECOPD has been gradually recognized and preliminarily explored. The clinical phenotype differentiated by peripheral eosinophils is one of the important phenotypes of AECOPD. Eosinophils are generally considered to be a type of white blood cell associated with allergic diseases. In allergic disease, YPF has been shown to have good effects in both improving symptoms and controlling relapses [18–20]. A number of studies have also shown that YPF inhibits eosinophil activity and also inhibits eosinophil proliferation [21, 22]. We hypothesized that YPF may have a more pronounced clinical benefit on the eosinophilic phenotype of AECOPD. Therefore, we designed a prospective, multicentre, randomized, double-blind, placebo-controlled clinical trial based on eosinophil phenotypic stratification to evaluate the efficacy of YPF on clinical symptoms and quality of life, safety, and therapeutic response in microecology and immunity in stable COPD. We hoped to confirm the preventive and trerapeutic effects of YPF from different perspectives and to discover its possible mechanism.

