### Outcome measurements

#### Efficacy indicators

The primary outcome is the changes in the COPD assessment test (CAT) score after 52-week of treatment. Specifically, the differences between the total CAT score at week 52 and baseline will be calculated respectively for the experimental and the control groups, respectively, and the difference between the two groups will be compared. The secondary outcomes include the following eleven indicators:Annualized rates of moderate or severe COPD exacerbations. The measure is the number of acute exacerbations of moderate or severe COPD during 52-week treatment/total participants in the group. The definition of an acute exacerbation of COPD (AECOPD): is an acute change in a patient’s baseline dyspnea, cough, and/or sputum beyond day-to-day variability sufficient to warrant a change in therapy. The severity of AECOPD is graded as follows: (1) Mild: requires only increased treatment with short-acting bronchodilators, such as short-acting β-receptor agonists (SABA); (2) Moderate: requires increased antibiotics and/or oral glucocorticoid hormone; (3) Severe: requires hospitalization or emergency treatment, may be complicated by acute respiratory failure.All-cause admission rate and admission rate due to acute exacerbation. All-cause admission rate = (total number of admission during 52-week treatment)/ (total number of participants in the group) and the admission rate due to acute exacerbation = (number of admission due to acute exacerbation during 52-week treatment)/ (total number of participants in the group).The changes in the St George's Respiratory Questionnaire (SGRQ) score.The proportion of patients with an SGRQ response (defined as an improvement of ≥ 4 units from baseline).The changes in the CAT score.The median time to the first exacerbation of COPD and the median time to the first exacerbation of moderate or severe COPD during treatment.Duration and time interval of acute exacerbations compared with the control group.Annualized rates of acute exacerbations of COPD of different severity.The changes in clinical symptom score (Table 2) compared with the control group.The changes in the individual clinical symptom score compared with the control group.Frequency of first-aid drug use.The changes in TCM constitution from the baseline to week 24 and week 52.

**Table 2 Tab2:** The clinical symptom assessment scale

Item	Symptoms Assessment rating scale			
	0 (none)	1 (mild)	2 (moderate)	3 (severe)

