### Statistical analysis

The SAS 9.4 statistical software will be used for statistical analysis. Both full analysis set (FAS) and per-protocol set (PPS) will be used for baseline and efficacy analysis, while the safety set (SS) for the safety analysis. Data will be descriptively analyzed and presented as means and standard deviations, medians and interquartile ranges, and frequencies. The minimum, maximum, P25, median, and P75 are given when necessary. All analyses will be two-sided, with a *p*-value of less than 0.05 considered statistically significant.

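### Log-rank and Cox comparisons of exacerbation duration and interval are made among patients selected by a post-randomisation event, so they do not compare the randomised arms

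*Protocol article*

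**What the plan says.** Among the secondary outcomes in the protocol article (Outcome measurements, Efficacy indicators) are two separate entries:

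- "The median time to the first exacerbation of COPD and the median time to the first exacerbation of moderate or severe COPD during treatment"
- "Duration and time interval of acute exacerbations compared with the control group"

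The Efficacy analysis section assigns methods outcome by outcome. For the second entry it states: "The duration and interval of AECOPD will be tested by the log-rank test, and the Cox proportional-hazards model will be used" to obtain a hazard ratio with its 95% confidence interval. It does not say when an interval starts, whether the patient or the episode is the unit, or how patients without an exacerbation enter the comparison. On analysis sets, the Statistical analysis section says: "Both full analysis set (FAS) and per-protocol set (PPS) will be used for baseline and efficacy analysis".

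Two other statements matter here. The Background reports that YPF, in the sponsor's earlier trial, "significantly reduced the risk of acute exacerbations by 32.3% in moderate-to-severe COPD patients". The inclusion criteria require, in the year before entry, "≥ 2 moderate acute exacerbations or ≥ 1 severe acute exacerbation".

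**The concern.** Randomisation protects a comparison only if everyone randomised can contribute to it. A patient with no exacerbation has no episode to time and no gap after one. Whether a patient exacerbates is itself an outcome that the trial expects YPF to change. If YPF prevents episodes mainly in the less frail, the YPF patients who still exacerbate are on average frailer than their control counterparts. A hazard ratio for duration or gap then mixes any drug effect with this difference in case mix, yet it would be reported as a treatment effect.

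Two further weaknesses follow from the stated method. If every episode is entered, a patient with several contributes correlated times, and a plain log-rank test or Cox model treats them as independent. The hazard ratio also points in opposite directions for the two measures: above 1 is favourable for duration (episodes end sooner), below 1 is favourable for interval (the next episode comes later).

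**Working it through.** **The plan's own figure.** The article gives no figure for duration, interval or time to first exacerbation. Its one sample-size calculation, for CAT, assumes a between-group difference that "was 2.2, and the combined standard deviation was 6.2184". Per arm, n = 2 × (1.960 + 0.842)² × 6.2184² / 2.2² = 125.4, so 126, or 252 in total. Then 126 / 0.8 = 157.5, so 158 per arm and 316 in total. This reproduces and is untouched by the point.

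**Inputs.** From the article: 158 per arm, 52 weeks of follow-up, and the 32.3% reduction, read here as a rate ratio of 1 − 0.323 = 0.677 (an assumption). The article gives no exacerbation rate, so the control rate r (0.5 to 2.0 per year) and the between-patient dispersion d (0, 0.5 and 1.0) are assumed.

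**Step 1: who has anything to analyse.** With yearly rate m, P(at least one) = 1 − exp(−m) when d = 0, and 1 − 1/(1 + m) when d = 1.

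| At r = 1.0 per year | Control | YPF (m = 0.677) |
|---|---|---|
| At least one exacerbation, d = 0 | 63.2% (100 of 158) | 49.2% (78 of 158) |
| At least one exacerbation, d = 1 | 50.0% (79 of 158) | 40.4% (64 of 158) |
| At least two (a completed gap), d = 0, 0.5 and 1 | 25–26% | 15–16% |

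Over r = 0.5 to 2.0 and all three dispersions, 33–86% of control and 25–74% of YPF patients would have a duration. The subsets differ in size between arms because of the drug effect itself.

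**Step 2: how the selected groups differ.** With d = 1, give each patient a gamma frailty with mean 1. Mean frailty among exacerbators is [1 − 1/(1 + m)²] / [m/(1 + m)] = 1 + 1/(1 + m). Control: 1 + 1/2 = 1.50. YPF: 1 + 1/1.677 = 1.596. The ratio is 1.596 / 1.50 = 1.064, so YPF exacerbators are about 6% frailer although the arms were equal at randomisation.

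**Step 3: effect on duration.** In a simulation with d = 1, r = 0.7, 1.0 and 1.5, and no true drug effect on duration:

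- Episode length unrelated to frailty: YPF/control ratio of mean duration 0.999–1.001.
- Length proportional to frailty to the power 0.3: 1.017–1.024.
- Length proportional to frailty to the power 0.5: 1.035–1.038 (at r = 1.0, 11.91 / 11.48 = 1.038).

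The spurious lengthening on YPF is therefore 0 to 4%.

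**Step 4: effect on interval.** Gamma-Poisson simulation with r = 0.8, 1.2 and 1.6, d = 0.5 and 1.0, and a true rate ratio of 0.677:

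| Cox analysis | HR, YPF vs control |
|---|---|
| Time to first exacerbation, all patients | about 0.70–0.76 |
| Gap after an exacerbation, open gaps censored at week 52 | about 0.69–0.81 |
| Completed gaps only | about 0.87–0.91 |

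A repeat run gave the same picture, with differences of about 0.02 or less from simulation noise. The rule for open gaps, which the article does not state, matters far more than the conditioning in this model.

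**The case against.** The strongest reply is that log-rank and Cox handle censored times, so the interval analysis need not lose the effect. This stands. A patient with exactly one exacerbation contributes a censored gap, and Step 4 then gives a hazard ratio close to the one for time to first exacerbation. A reader might infer that intervals are available only from patients with two episodes, or that a one-third reduction would all but vanish. Neither follows from the stated method; the strong shrinkage appears only if open gaps are discarded, which the article does not say will happen.

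*Interval* is also undefined. If it runs from randomisation to the first exacerbation with censoring, that half of the point falls away. The outcome list gives time to first exacerbation its own entry, however, so the gap reading is the more natural one. Likewise, the correlation problem arises only if episodes are the unit.

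A reader might also infer that time to first exacerbation will have no test and only a median. The article is silent on a test for it; a full analysis plan may supply one, and silence is not a decision against testing. Nor can it be said that the median will go unreached. With dispersion 0, 0.5 and 1.0, an arm's own rate must reach 0.69, 0.83 and 1.00 per year, and for the YPF arm the control rate must reach 0.69/0.677 = 1.02, 0.83/0.677 = 1.22 and 1.00/0.677 = 1.48. The article gives no rate, and the population is enriched for exacerbations.

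None of this answers the conditioning in the duration comparison, or in the interval comparison read as a gap.

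**Conclusion.** The point holds in a limited form. The article fixes a between-arm hazard ratio for duration, and for interval as most naturally read, in patients selected by an event the treatment is expected to change. That is not a comparison of the randomised arms, whatever the size of the bias.

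The size is probably modest: 0 to 4% on mean duration, and little distortion of the interval hazard ratio if open gaps are censored. If only completed gaps are used, the hazard ratio moves to about 0.87–0.91 against a true rate ratio of 0.677. These figures rest on assumed rates and dispersions, on reading 32.3% as a rate reduction, and on a gamma-frailty model. They do not support a claim that the duration result would be seriously misleading. Only secondary outcomes are affected; the CAT primary outcome and the sample size are not. The change should be made because it is cheap and because the data for the all-patient measures are already collected.

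**What to change.** Settle the following before unblinding:

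1. Apply the log-rank test and Cox model, stratified by the eosinophil randomisation group, to time to first exacerbation (any severity, and moderate or severe) in all randomised patients. Censor patients without an exacerbation at the end of their follow-up.
2. Replace the interval test by a recurrent-event model with robust variance on all patients.
3. Replace the duration test by exacerbation days per patient-year, counting zero for patients with none.
4. Show episode length and gaps among exacerbators descriptively only. Define when a gap starts and how open gaps are presented.

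The schedule of assessments already records the number and duration of exacerbations at each follow-up visit, with an additional visit at onset, so no new data are needed. The cost is wording and a little more analysis work, and episode length no longer gets its own p-value. Time to first exacerbation may not reach 80% power: a hazard ratio of 0.677 needs about 207 events. At a control rate of 1.0 per year the trial would yield about 79 + 64 = 143 (d = 1) to 100 + 78 = 178 (d = 0). For a secondary outcome this is a reason to report the confidence interval, not an obstacle.

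### Score changes, including the CAT change that is the primary outcome, are assigned to a log-rank test and Cox model, although the outcome is defined and the trial sized as a comparison of means

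*Protocol article*

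**What the plan says.** Three sections of the protocol article bear on this point.

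- **Outcome measurements, Efficacy indicators.** "The primary outcome is the changes in the COPD assessment test (CAT) score after 52-week of treatment". The text then specifies that "the differences between the total CAT score at week 52 and baseline will be calculated respectively for the experimental and the control groups", and that "the difference between the two groups will be compared". CAT change also appears a second time, in the list of secondary outcomes.
- **Sample size.** Citing the previous study, "the mean difference in CAT scores between the YPF group and the control group was 2.2" and "the combined standard deviation was 6.2184". The calculation is made "with an α risk of 0.05 and a β risk of 0.2 in a two-sided contrast". It gives 252 evaluable subjects and, with 20% attrition, 316 (158 per arm).
- **Statistical analysis, Efficacy analysis.** The section opens by saying that the method follows the type of variable. It gives log-rank and Cox to the duration and interval of exacerbations. Its last sentence begins: "The changes in the CAT score, the SGRQ score, the clinical symptom score, and the single clinical symptom score will also use the log-rank" test. To its end, that sentence says that these score changes "will also use the log-rank test and the Cox proportional-hazards model for analysis".

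No other section names a method for change in CAT. The t-test and non-parametric wording stands under Demographic and baseline analysis and concerns the baseline comparison.

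**The concern.** A change score is a continuous value read at a fixed visit. It is not a time to an event, it can be negative, and in CAT a negative change is an improvement. Log-rank and Cox methods need an event, a time origin and a censoring rule, and the article defines none of these for any score. The outcome definition and the sample size therefore describe one analysis and the efficacy section another.

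Followed as written, the inferential result for CAT would be a hazard ratio. That cannot be set against the planned 2.2 points and carries no confidence interval in CAT units. An analyst would also have to invent the event, which turns the primary outcome into a different one. The same sentence affects SGRQ and all the symptom scores.

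Timing adds to this. The section on randomization, blinding and unblinding places the analysis after database lock and unblinding. A method corrected at that stage would be open to the charge that it was chosen after seeing the data.

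**Working it through.** **1. Reproduce the stated sample size.** Inputs from the Sample size section: difference 2.2, SD 6.2184, two-sided α 0.05, β 0.2. Allocation is 1:1.

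- n per arm = 2 × (1.96 + 0.8416)² × (6.2184 / 2.2)² = 125.4, so 126 per arm and 252 in total.
- Attrition: 126 / (1 − 0.20) = 157.5, so 158 per arm and 316 in total.
- Power at 126 per arm: 80.2% (normal approximation), 79.9% (t-test).

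Both stated totals come out exactly. The trial is sized for a two-sample comparison of means.

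**2. Can a log-rank power be derived from the article?** No. It gives no hazard ratio, event or event count for CAT. Any figure below rests on assumptions and serves only to show the spread.

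**3. Reading A: the raw change score is used as the 'time', with nobody censored.** The log-rank test is then a rank test. With 126 per arm, a 2.2-point shift and SD 6.2184, simulated power is about 68–77%, against 80% for the t-test.

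**4. Reading B: time to first CAT improvement of at least 2 points**, assessed at weeks 4, 12, 24, 36 and 52. The threshold is assumed. There are 126 per arm and the total SD is 6.2184. The main runs assume a control mean change of −1 and a within-subject correlation of 0.3–0.7. A second set assumes a control mean change of 0 and a within-patient SD of 4.4, which is a correlation of 1 − 4.4²/6.2184² = 0.50.

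| True effect | t-test at week 52 (second set) | Log-rank (main runs) | Log-rank (second set) |
|---|---|---|---|
| Constant 2.2 | 82% | about 70–80% | 79% |
| Builds up to 2.2 at week 52 | 79% | about 15–19% (linear) | 12% (0, 0, 0.7, 1.5, 2.2) |
| Early, gone by week 52 (true difference 0) | 5% | about 58–72% | 55% (2.2, 2.2, 1.5, 0.7, 0) |

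The last row depends on how the effect fades. A repeat with the profile 2.2, 2.2, 1.5, 0.7, 0 and a control mean change of −1 (500 trials per setting) gave 67%, 56% and 49% at correlations 0.3, 0.5 and 0.7.

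The bottom two rows carry the argument. A time-to-first-improvement analysis can miss a week-52 difference that exists and can declare a benefit when the week-52 difference is zero. It answers a different question from the one in the outcome definition.

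**5. After the correction.** With a comparison of mean change, 252 evaluable and 316 randomised stand. If 6.2184 is the SD of an unadjusted score, baseline adjustment with an assumed correlation of 0.3, 0.5 or 0.7 gives 83.7%, 90.0% or 97.6% power at 126 per arm.

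**The case against.** Four points can fairly be made on the other side.

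- **The sentence may not concern the primary outcome.** CAT change is listed twice, and the sentence places it beside SGRQ and symptom-score changes, which are all secondary. This reading is open. It leaves the primary outcome with no named method and the secondaries with an unsuitable one, so the correction is the same.
- **A reader might infer that the named methods cannot test a group difference at all, or that the analysis cannot be run.** The documents do not support that. Reading A can be run, detects a shift between groups and loses only modest power. What it lacks is an estimate in CAT points with a confidence interval.
- **Mean changes would still be reported.** The Statistical analysis section promises means and standard deviations. That is descriptive only, with no inferential estimate of the difference.
- **The analysis plan may settle it.** An article may leave the method to a fuller document. This one does not leave it open: it names a method, and that method does not fit the outcome. A plan that compared means would contradict the published text, and a plan that followed it would inherit the mismatch.

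**Conclusion.** The point stands as an analysis that is wrong as written. The mismatch between outcome definition, sample size and method rests on the article's own text and needs no assumption.

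Its numerical consequence does need assumptions, and no single power figure should be quoted. Power ranges from nearly the planned 80% (raw change scores, or a constant effect from the first visit) down to about 12–19% (an effect that builds up by week 52). With an early effect that has gone by week 52, rejection is about 49–72% where 5% is intended. A reader might infer from the low figures that the trial is underpowered. The documents do not support this: the article defines no event, so none of these readings is its stated plan, and the planned size is adequate for the comparison of means it was computed for.

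**What to change.** Replace the last sentence of the Efficacy analysis section. State that changes in CAT, SGRQ, total symptom score and single symptom scores are compared between groups as mean change from baseline at week 52, reporting the mean difference with its 95% CI and p-value.

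One suitable form is ANCOVA with treatment, baseline score and eosinophil stratum (the randomisation factor). A repeated-measures mixed model that adds visit and treatment-by-visit, with the week-52 contrast as the result, would serve equally. The choice is the sponsor's. Say explicitly that the method applies to the primary CAT outcome as well as to the secondary listing.

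Confine log-rank and Cox to the exacerbation outcomes that are times. The analysis already stated for exacerbation duration and interval is not challenged by this point.

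The cost is a wording change, to be made and dated before database lock and unblinding. It needs no additional subjects, visits or data, and the sample size stays at 252 evaluable and 316 randomised.
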